**Figure 3 Fig3:**
[figure not shown]
**A representative example of a patient with inducible ischemia in perfusion CMR.**
**(A)** Stress perfusion **(B)** Rest perfusion. Red arrow indicates inducible ring-type ischemia in stress perfusion CMR.

##### Semi-quantitative analysis

Semi-quantitative analysis will be performed by signal intensity (SI)/time curves with a commercially available software (QMass MR Enterprise Solution, Advanced Edition, Medis, Leiden, the Netherlands); endocardial and epicardial borders of the three slices are traced manually, and curves and bull’s eye plots will be obtained by two independent skilled operators, with divergences being resolved by consensus.

### Echocardiography

Two-dimensional transthoracic echocardiography (TTE) will be performed at patient’s screening and 12 weeks after enrolment. TTE will be performed with a commercially available echocardiographic instrument (Vivid 7, GE Medical Systems, Milwaukee, Wisconsin, United States or Sequoia 512, Acuson, Mountain View, California, United States). A standard M-mode, two-dimensional ECG and echocardiographic Doppler study will be performed. All TTE recordings will be interpreted by staff cardiologists.

### Follow-up

All patients will visit our outpatient clinic at 1, 4, 8, 12, and 16 weeks after randomization. Each visit consists of a clinical evaluation, blood analysis, and a 12-lead ECG. After three months of udenafil treatment, adenosine-stress CMR, echocardiography, and a stress test will be performed (Table 3).

**Table 3 Tab3:** **Trial process chart**

Visit	Visit 1	Visit 2	Visit 3	Visit 4	Visit 5	Visit 6	Visit 7
Status	Screening	Baseline					Follow-up phase
Week	−4 ~ 0	0	1 (±3 day)	4 (±7 day)	8 (±7 day)	12 (±7 day)	16
Informed consent	●						
Inclusion/exclusion criteria	●						
Baseline characteristics	●						
Risk factors	●						
Medical history	●						
Past medication history^1^	●						
Family history	●						
Randomization		●					
Physical examination	●					●	
Vital signs	●	●		●	●	●	
Height/weight^2^	●	●		●	●	●	
Blood analysis^3^	●					●	
Pregnancy test^4^	●					●	
ECG	●					●	
Echocardiography	●					●	
Exercise test	●					●	
CMR^5^	●					●	
CAG or CCTA	●						
SF-36 questionnaire	●					●	
BISF-W self-assessment questionnaire	●					●	
Case drug distribution		●		●	●		
Case drug collection				●	●	●	
Trial evaluation							
Adverse events	●	●	●	●	●	●	●
Patient’s compliance			●	●	●	●	
Concomitant medications^6^		●	●	●	●	●	

CMR; Cardiac magnetic resonance image, CAG; Coronary angiography, CCTA; Coronary CT angiography, ECG; Electrocardiogram.

^1^The participant’s usual medication regimen continued unchanged throughout study duration.

^2^Check weight only after Visit 2.

^3^CBC: WBC, Hemoglobin, Hematocrit, Platelet; Chemistry: Total protein, Albumin, Globulin, Total bilirubin, AST; aspartate aminotransferase, ALT; alanine transaminase, ALP; alkaline phosphatase, BUN; blood urea nitrogen, Creatinine, Uric acid; Electrolyte: Na, K, Cl; NT-proBNP; N-terminal of the prohormone brain natriuretic peptide; hs-CRP; high-sensitivity c-reactive protein.

(NT-proBNP, hs-CRP: check visit 1 and visit 5).

^4^Women of child-bearing age.

^5^Stop all medications three days before CMR.

^6^Concomitant medications: beta-blockers, calcium channel blockers, angiotensin converting enzyme inhibitors, angiotensin receptor blockers, statin, and trimetazidine.

During follow-up visits all adverse events including chest pain, headache, and so forth, will be documented. Serious adverse events will be immediately reported to the principal investigator. To ensure the quality of this trial, the clinical monitors will survey and document the trial process once a month in each participating hospital. Patient dropouts and the reasons, and patients’ compliance will be recorded at three months after randomization.

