### Endpoints

The primary endpoint is a >25% improvement from baseline in perfusion defect size in adenosine-stress CMR after three months of udenafil treatment. The secondary endpoints include a <25% improvement in perfusion defect size, chest pain, quality of life, and sexual functions after three months of udenafil treatment. Detailed endpoints are listed in Table 1.

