**Table 1 Tab1:** **Endpoints**

	Endpoint details
Primary endpoint	>25% improvement in perfusion defect size in adenosine-stress CMR from baseline to three months after udenafil treatment
Secondary endpoints	<25% improvement in perfusion defect size in adenosine-stress CMR from baseline to three months after udenafil treatment
	Decrement of frequency of chest pain
	Improvement of ST-depression in stress test
	Improvement of Duke score in stress test
	Improvement of QoL assessment by SF-36 questionnaire
	Improvement of sexual dysfunction assessment by BISF-W self-questionnaire
	Improvement of biomarkers for endothelial function

CMR*;* Cardiac magnetic resonance image, QoL; Quality of life.

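### The blood and ECG schedule contradicts itself between the Follow-up text, Table 3 and footnote 3, and the second NT-proBNP/hs-CRP sample is placed at week 8, away from the week-12 outcome assessments

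*Protocol article*

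**What the plan says.** Three places in the protocol article fix when blood is taken, and two of them fix when an ECG is recorded.

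- **Follow-up section.** Visits take place 1, 4, 8, 12 and 16 weeks after randomization, and "Each visit consists of a clinical evaluation, blood analysis, and a 12-lead ECG". The section then cites Table 3.
- **Table 3, rows.** The row labelled "Blood analysis^3" and the ECG row are each marked at Visit 1 (screening) and Visit 6 (week 12) and nowhere else.
- **Table 3, footnote 3.** After itemising the blood panel, the footnote adds "NT-proBNP, hs-CRP: check visit 1 and visit 5". Table 3 places Visit 5 at week 8.

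Two secondary endpoints in Table 1 bear on the same chart: "Decrement of frequency of chest pain" and "Improvement of biomarkers for endothelial function". The Endpoints section gives a time for the first, listing "chest pain, quality of life, and sexual functions after three months of udenafil treatment". Neither that section nor Table 1 gives a time for the biomarkers. On chest pain, the text below Table 3 says "During follow-up visits all adverse events including chest pain, headache, and so forth, will be documented".

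**The concern.** A site that follows the Follow-up text draws blood and records an ECG at five post-baseline visits. A site that follows Table 3 does so at one. Two centres take part, so the laboratory and ECG safety data reaching the monitoring board could differ by site in how often patients were examined. Within a site both arms share the same schedule, so the contrast between arms is not biased by this alone. However, the number of abnormalities found depends on the number of looks, and a pooled safety table would mix unequal ascertainment.

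Footnote 3 raises a second problem. NT-proBNP and hs-CRP are the only markers listed beyond routine haematology, chemistry and electrolytes. Their second sample is assigned to a visit at which the footnote's own row shows no blood draw and Table 3 marks no imaging, exercise test or questionnaire. Any change in these markers would then be measured over a different period from the outcomes it might be set against.

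**Working it through.** No stated figure is at issue here, so the check sets the schedules side by side.

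| Visit (week) | Blood and ECG, Follow-up text | Blood and ECG, Table 3 rows | NT-proBNP and hs-CRP, footnote 3 |
|---|---|---|---|
| 1 (screening) | not addressed | marked | yes |
| 2 (0) | not addressed | – | – |
| 3 (1) | yes | – | – |
| 4 (4) | yes | – | – |
| 5 (8) | yes | – | yes |
| 6 (12) | yes | marked | – |
| 7 (16) | yes | – | – |

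**Size of the disagreement.**
- Post-baseline occasions per patient: 5 by the text (weeks 1, 4, 8, 12, 16) and 1 by Table 3 (week 12).
- Over the planned 80 patients with full attendance: 5 × 80 = 400 against 1 × 80 = 80, a difference of 320 blood draws and 320 ECGs.

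**Timing of the markers.**
- Nominal gap between footnote 3 and the week-12 visit: 12 − 8 = 4 weeks.
- Table 3 allows ±7 days at both visits, so Visit 5 spans weeks 7 to 9 and Visit 6 spans weeks 11 to 13. The gap can run from 11 − 9 = 2 weeks to 13 − 7 = 6 weeks. The windows do not overlap, so visit tolerance cannot reconcile the two.

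**What each reading yields for the markers.**
- If the Table 3 row governs, blood is drawn at week 12 but not at the visit the footnote names.
- If the Follow-up text governs, blood is drawn at week 8, but the footnote still assigns no marker sample to week 12.
- If the footnote is taken alone, the second value is at week 8.

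So footnote 3 provides no week-12 value whichever other statement it is combined with.

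**Secondary endpoints against Table 3.**

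| Secondary endpoint | Matching row | Marked at |
|---|---|---|
| Smaller perfusion improvement | CMR | Visits 1 and 6 |
| Chest-pain frequency | none printed | – |
| ST depression | Exercise test | Visits 1 and 6 |
| Duke score | Exercise test | Visits 1 and 6 |
| SF-36 | SF-36 | Visits 1 and 6 |
| BISF-W | BISF-W | Visits 1 and 6 |
| Endothelial biomarkers | none identified | – |

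Five of the seven have a source at both times. The other two have no identified source in the chart as printed.

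**The case against.** The strongest reply is that this is a journal article, which condenses a fuller protocol. That reply does not dispose of the schedule conflict. The Follow-up section points to Table 3, and footnote 3 is attached to the row it contradicts. Condensing explains missing detail; it does not explain printed statements that disagree.

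A numbering slip is possible. If screening and baseline were counted as one visit, the fifth visit would be week 12. That is conjecture, and Table 3 as printed puts Visit 5 at week 8.

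The reply carries more weight against stronger readings that a reader might infer:

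- **That two secondary endpoints cannot be analysed.** The documents do not support this. A diary, recall question or assay panel may stand in the full protocol or case report form, neither of which is shown.
- **That chest pain has no baseline and is recorded only as harm.** The row "Adverse events" is marked at Visits 1 and 2 as well as later, medical history and baseline characteristics are taken at Visit 1, and chest pain is an entry criterion. None of these is said to record a frequency, but a baseline count cannot be ruled out. Nor does the article say that adverse-event reports are the source of the efficacy endpoint.
- **That NT-proBNP and hs-CRP are the endothelial biomarkers, and the wrong ones.** The article never gives them that role. They appear in a footnote to a general blood panel.
- **That the footnote schedules a sample where no blood is taken.** This is true of the Table 3 row but contradicted by the Follow-up text. It is an unresolved conflict, not a proven missing sample.
- **That a week-8 sample breaches the biomarker endpoint's definition.** No time point is printed for that endpoint. What can be said is that week 8 is out of step with every other scheduled outcome assessment.

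**Conclusion.** The point holds as an internal contradiction. Blood analysis has three incompatible schedules and the ECG has two. The difference is 5 against 1 post-baseline occasions per patient, or 400 against 80 in total, assuming 80 patients who attend every visit. Footnote 3 places the second NT-proBNP and hs-CRP sample nominally four weeks before the week-12 assessments, outside any allowed visit window.

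The counts describe the blood and ECG conflict only; they say nothing about whether any endpoint can be delivered. The primary endpoint, its test and the sample size are untouched. The matter deserves correction because it changes what is collected, not because it threatens the main result.

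The absence of a printed measure for chest-pain frequency and for endothelial biomarkers is a secondary note. It calls for a check against the full protocol and is not, on this document, a demonstrated defect.

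**What to change.** 1. Make footnote 3 agree with the Blood analysis row, so that the second NT-proBNP and hs-CRP sample falls at Visit 6 (week 12) with the other outcomes. Table 3 already marks a blood draw there, so no visit or extra draw is needed.
2. Reconcile the Follow-up text with the Blood analysis and ECG rows of Table 3. How often safety bloods and ECGs are taken is for the investigators to decide; the need is for one schedule that both centres follow. Cost: a wording change if the table stands, or up to 4 more blood draws and ECGs per patient than the table shows if the text stands.
3. Recruitment was already under way when the article was written, so establish which schedule each centre has been using. Keep any week-8 marker values and report them as week-8 values.
4. Confirm in the full protocol and case report form that chest-pain frequency and the endothelial biomarkers each have a named measure at baseline and at three months. If they do, add the rows to Table 3. If they do not, the gap needs an amendment.

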**Table 2 Tab2:** **Inclusion and exclusion criteria**

**Inclusion criteria**	
1	MVA patients with typical symptom and positive adenosine-stress CMR and with normal coronary artery in CCTA or coronary angiography.
2	Definition of positive adenosine-stress CMR: perfusion defect >25% of transmurality (by two radiologists based on visual assessment and qualitative assessment in core-lab)
3	Gender: female
4	Age: 18 to 80-years-old

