**Exclusion criteria**	
1	Patient has a contraindication to CMR contrast media or CMR imaging
2	LVEF <50%
3	Any heart rhythm abnormality other than sinus rhythm
4	Valvular heart disease with more than moderate degree
5	Renal failure
6	Congestive heart failure
7	Myocardial infraction
8	Myocarditis
9	Congenital heart disease
10	Pericarditis
11	Variant angina (positive provocation test with ergonovine or acetylcholine)
12	GERD (conformed by esophagogastroduodenoscopy)
13	Pregnant women, suspected pregnant women or lactating women
14	QT prolongation syndrome or taking drugs that prolong the QT interval:
	- Antiarrhythmics class IA; quinidine, procainamide
	- Antiarrhythmics class III; amiodarone, sotalol
15	Pre-analytical within 30 days of screening in a clinical trial that may affect the influence of udenafil:
	- Other PDE-5 inhibitors (for example sildenafil, tadalafil)
	- Nitrates/NO donor (for example nitroglycerin, isosorbide mononitrate, isosorbide dinitrate, amyl nitrate/nitrite, sodium nitroprusside, and nicorandil)
16	Pre-analytical within seven days of screening in a clinical trial that may affect the metabolism of udenafil:
	- Antibacterials (for example erythromycin)
	- Antifungals (for example itraconazole, ketoconazole)
	- Antivirals (for example ritonavir, saquinavir, amprenavir, indinavir, nelfinavir)
	- Cimetidine
	- Grapefruit juice
17	Allergy or sensitivity with PDE-5 inhibitors

CCTA; Coronary CT angiography, CMR; Cardiac magnetic resonance image, GERD; Gastroesophageal reflux disorder, LVEF; Left ventricular ejection fraction, MVA; Microvascular angina, NO; Nitric oxide, PDE-5; Phosphodiesterase-5.

If all of the inclusion criteria are met and none of the exclusion criteria apply, the patient will be required to provide written informed consent, as required by the institutional review board (Samsung Medical Center Institutional Review Board, Seoul National University Bundang Hospital Institutional Review Board) in accordance with the Declaration of Helsinki.

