### Randomization and interventions

After the patients are enrolled in the study, the patients will be randomized to the udenafil treatment group or the placebo group by a web-based computerized program which will be independently managed at T&W software (Three and Water software, Seoul, Republic of Korea). The flowchart of the study design is shown in Figure 1.

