### Udenafil treatment protocol

After random assignment, patients in the udenafil treatment group will receive 100 mg udenafil daily (Dong-A Pharmaceutical, Seoul, Republic of Korea) for three months. Since headache and facial flushing are common side effects of udenafil, the dose of study medication will be reduced by 50% if severe headache develops. In patients with serious side effects the study medication will be stopped.

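### Table 3 schedules no pregnancy test at Visit 2, so women of child-bearing age can be randomised and first supplied with study drug on a negative result up to 28 days old

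*Protocol article*

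**What the plan says.** Table 2 of the Protocol article restricts entry to women, with the age criterion "Age: 18 to 80-years-old". Exclusion criterion 13 reads "Pregnant women, suspected pregnant women or lactating women". The sentence after Table 2 makes consent follow once eligibility is settled: "If all of the inclusion criteria are met and none of the exclusion criteria apply".

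Table 3 (Trial process chart) fixes the timing:

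- The row "Inclusion/exclusion criteria" is marked at Visit 1 only (screening, week -4 to 0).
- The pregnancy-test row is marked at Visits 1 and 6. Footnote 4 limits it to "Women of child-bearing age".
- Randomisation is at Visit 2 (baseline, week 0). Study drug is distributed at Visits 2, 4 and 5.

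The section Randomization and interventions says only "After the patients are enrolled in the study, the patients will be randomized to the udenafil treatment group or the placebo group". The treatment section continues: "After random assignment, patients in the udenafil treatment group will receive 100 mg udenafil daily". The Follow-up section lists visits that begin after randomisation: "All patients will visit our outpatient clinic at 1, 4, 8, 12, and 16 weeks after randomization".

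**The concern.** The protocol makes pregnancy a bar to entry, but its visit chart does not confirm that the bar is respected when treatment begins. Pregnancy status can change between screening and baseline, and the screening window lets up to four weeks pass. A woman who conceives in that window meets exclusion 13 on the day she is randomised, yet nothing scheduled for that day would show it.

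If she is missed at Visit 2, she is supplied with drug there and again at Visits 4 and 5. The next scheduled test is at Visit 6, when drug is collected and none is given out. That test can record an exposure but cannot prevent it.

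The basis is the protocol's own exclusion criterion. The document gives no data on reproductive hazard with udenafil, and none is assumed here.

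**Working it through.** The plan states no figure to reproduce. The check is a column-by-column reading of Table 3, followed by interval arithmetic.

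**Reading the columns.** The seven columns are Visits 1 to 7. The echocardiography and CMR rows confirm the alignment: both are marked at Visits 1 and 6. The Echocardiography section places echocardiography at screening and 12 weeks, and the Follow-up section places CMR after three months of treatment.

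| Row in Table 3 | V1 (wk -4 to 0) | V2 (wk 0) | V4 | V5 | V6 (wk 12 ± 7 days) |
|---|---|---|---|---|---|
| Eligibility criteria | yes | – | – | – | – |
| Pregnancy test | yes | – | – | – | yes |
| Randomisation | – | yes | – | – | – |
| Drug distribution | – | yes | yes | yes | – |
| Drug collection | – | – | yes | yes | yes |

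None of these rows is marked at Visit 3 or Visit 7.

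**Does another section supply the check?**

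- The text after Table 2 places eligibility before consent and mentions no later confirmation.
- The randomisation section goes from enrolment to allocation and names no re-check.
- The Follow-up section describes a clinical evaluation and blood sampling at each visit, but its visits start at week 1, so Visit 2 is not among them.
- The blood panel in footnote 3 contains no pregnancy marker.

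**Age of the last scheduled result at randomisation and first supply**

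- Screening at week 0: 0 × 7 = 0 days.
- Screening at week -4: 4 × 7 = 28 days.

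**Interval from Visit 2 to the next scheduled test (Visit 6)**

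- Earliest: 12 × 7 − 7 = 77 days (11 weeks).
- Latest: 12 × 7 + 7 = 91 days (13 weeks).

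**Longest interval between the two scheduled tests**

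- 28 + 91 = 119 days = 17 weeks.

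**Who could be affected**

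- Only women of child-bearing age whose screening test was not done on the day of Visit 2.
- Active exposure is possible only in the udenafil arm, 40 of the 80 planned patients.
- The age distribution is not given, so no patient count can be derived.

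**Upper bound on added tests**

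- 80 randomised women × 1 test = 80. This would require every woman to be of child-bearing age and none to be tested on the day.

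**The case against.** The strongest reply is that nothing here is contradicted. Exclusion 13 bars pregnant women, the chart tests the relevant women before treatment, and the document nowhere promises a check at randomisation. It also sets no limit on how old a screening test may be. On that view the point is only a preference for tighter practice. The article is also a condensed account, and a same-day eligibility confirmation could be in the full protocol, as contraception and withdrawal rules may be. A blank cell in a summary chart is weaker evidence than a statement that no check is made.

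Part of this stands. The full protocol may contain a baseline check, and the supporting text adds little beyond not filling the gap. Visit 2 is also a real clinical contact: vital signs, weight, adverse events and concomitant medications are marked there, and exclusion 13 covers suspected pregnancy, which an investigator may raise without a test.

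The main objection does not hold. The chart is not silent on the matter. It has a row for the pregnancy test and states at which visits the test is done, and it gives Visit 2 its own list of procedures without this one. A screening interval of 28 days is within the stated window, so the gap arises from following the chart exactly.

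It could also be said that the 77 to 91 days overstate the problem, since a Visit 2 test leaves the interval to Visit 6 unchanged. That is true for women who conceive after Visit 2, and they are outside this point. For a woman already pregnant at Visit 2, those days are the possible exposure that a test detecting the pregnancy would prevent.

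**Conclusion.** The concern holds. As printed, Table 3 allows randomisation and first dispensing on a pregnancy result 0 to 28 days old, and the next scheduled test follows 77 to 91 days after Visit 2. A woman who conceived between screening and baseline could be entered against exclusion 13 and supplied with drug throughout the treatment period.

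This is a limited point of participant protection that should be corrected. The gap is zero for anyone tested on the day of Visit 2, and the expected number of cases is small. Sample size, error rate and analysis are untouched. The conclusion assumes that the chart is followed as written and that the full protocol, which is not shown, adds no baseline test.

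**What to change.** In Table 3, mark the pregnancy-test row at Visit 2 for women of child-bearing age whose screening test was not done that day. Amend footnote 4 to require a negative result before randomisation and first dispensing. The age of the last scheduled result at randomisation then falls from 0–28 days to 0 days.

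The cost is one low-cost test per woman concerned, at most 80 in the whole trial, using a test already in the protocol at a visit already attended. The drawbacks are minor inconvenience and a short wait for the result before allocation. The Trial status section reports recruitment as ongoing, so the change could still protect women not yet randomised. If the full protocol already requires this test, only the chart needs correcting.

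Tests at Visits 4 and 5 are optional and best decided together with the full protocol's contraception and withdrawal rules.

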## Background

Microvascular angina (MVA), also known as cardiac syndrome X, is characterized by anginal chest pain, an abnormal stress test indicative of myocardial ischemia, and normal coronary arteries on angiography. The condition is not as benign as originally reported. While patients with stable MVA have an excellent prognosis [1], unstable MVA patients presenting with acute coronary syndrome have an increased risk of death or myocardial infarction [2]. Women are more affected than men. The current therapeutic options for MVA are limited.

An impairment of endothelium-dependent vasodilation due to reduced nitric oxide (NO) release mainly accounts for the proposed mechanisms of MVA [3]. NO availability plays a critical role in the regulation of microvascular endothelial functions and the arterial structure [4–6]. Many of the biological actions of NO are mediated by 3’5’-guanosine monophosphate (cGMP), which is rapidly degraded by cGMP phosphodiesterase (PDE). Recently, phosphodiesterase-5-inhibitor (PDEi) has been reported to improve the endothelial function in animal and clinical studies [7–10]. PDE inhibitors improve cardiac performance in patients with heart failure [11] and reduce infarct size and attenuate cardiac dysfunction after ischemia/reperfusion injury or permanent coronary artery occlusion [12]. While short-term cardiovascular effects of PDE inhibitors have been studied, the effects of chronic PDEi administration are not well known, especially in women with MVA.

In the ‘Understanding of Chest Pain in Microvascular Disease Proved by Cardiac Magnetic Resonance Image: (UMPIRE)’ study, we tested whether udenafil offers benefits in the treatment of female MVA patients who have a documented perfusion defect in CMR.

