### Rationale for the udenafil dosage in MVA patients

Udenafil (Zydena™) was developed in 1997 and, after clinical trials, the drug was approved by the Korea Food and Drug Administration (KFDA) in 2005. The commercially available and clinically used doses are 100 mg and 200 mg daily. Its half-life time is between 11 and 13 hours, and the estimated duration of action is approximately 24 hours. Thus, udenafil may be a good candidate drug for chronic use due to its favorable pharmacokinetic properties among PDE-5 inhibitors (sildenafil: T1/2 = 2 hours, duration of action = 4 to 8 hours; tadalafil: T1/2 = 17.5 hours, duration of action = 36 hours). In phase 3 clinical studies [21], the 100 mg and 200 mg doses showed similar efficacy (81 versus 88.5%). However, the side effect rate was lower with 100 mg daily dosing (flushing: 10 versus 23%, headache: 0 versus 23%, chest discomfort: 0 versus 5.4%, and so on).

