### Rationale for the safety of udenafil use in MVA patients

A preclinical trial or phase 1 trial with PDE-5 inhibitors in coronary vasculature would minimize the risk of potential candidates being exposed to unnecessary risk. However, there are plenty of studies reporting the safe use of PDE-5 inhibitors in humans, including those evaluating the effect of PDE-5 inhibitors on the coronary arteries in humans[10–12]. There exist at least 11 isoforms of PDE, and the differential distribution of PDE isoforms in various tissues is the basis for the potential tissue-specific effect of a PDE inhibitor. Various tissues have different PDE isoform activities. Corpus cavernosum contains high activities of PDE isoforms 2, 3, and 5; human pulmonary circulation has PDE isoforms 1, 3, 4, and 5; and coronary arteries have PDE isoforms 1, 2, 3, 4, 5 [22]. Consequently, human coronary arteries can be a target of PDE-5 inhibitors.

In clinical trials, sildenafil contributes little to the increase in myocardial flow that occurs during exercise or reactive hyperemia [23], but coronary hemodynamics and circulation are not unfavorably altered after treatment with sildenafil and other PDE-5 inhibitors. These study results imply that PDE-5 inhibitors are safe, but less likely to be effective. Nevertheless, in patients with endothelial dysfunction, the PDE-5 inhibitors would lead to significant hemodynamic improvement. In dysfunctional endothelium, the release of NO by the endothelium is significantly compromised [24]. Halcox *et al*. [25] demonstrated that coronary arterial segments with endothelial dysfunction dilated significantly after application of acetylcholine combined with sildenafil. This finding infers that the inhibition of cGMP breakdown by PDE-5 inhibitors may, at least in part, compensate for reduced NO-related cGMP production due to endothelial dysfunction. Consequently, in patients with MVA with endothelial dysfunction the administration of PDE-5 inhibitors may significantly restore the NO-dependent vasodilation, leading to symptom improvement and improved perfusion in CMR.

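### Table 3 footnote 5 does not exempt udenafil/placebo from the three-day medication stop, so a literal reading puts the only post-baseline primary-endpoint scan about 72 hours after the last dose

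*Protocol article*

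**What the plan says.** Table 3 schedules CMR twice, at Visit 1 (screening) and Visit 6 (week 12, plus or minus 7 days). One footnote covers the whole row: "Stop all medications three days before CMR". Footnote 1 to the same table says the participant's "usual medication regimen continued unchanged throughout study duration".

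The Visit 6 scan carries the primary analysis. The Endpoints section says: "The primary endpoint is a >25% improvement from baseline in perfusion defect size in adenosine-stress CMR after three months of udenafil treatment". The Follow-up section matches this: "After three months of udenafil treatment, adenosine-stress CMR, echocardiography, and a stress test will be performed". The Udenafil treatment protocol section gives 100 mg daily for three months and refers to the product as study medication. Table 3 uses a different label, as in the row "Case drug distribution", which has its first dot at Visit 2.

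On pharmacokinetics, the dosage rationale states: "Its half-life time is between 11 and 13 hours, and the estimated duration of action is approximately 24 hours".

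**The concern.** The footnote is an instruction to sites, and its wording covers every medication. The article has narrower terms available: footnote 1 speaks of the usual regimen and footnote 6 names background drug classes. Footnote 5 uses neither. A coordinator who follows it to the letter would stop udenafil or placebo three days before the Visit 6 scan.

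That would change what the primary endpoint measures. The safety rationale proposes that "the administration of PDE-5 inhibitors may significantly restore the NO-dependent vasodilation, leading to symptom improvement and improved perfusion in CMR", by inhibiting cGMP breakdown. Any part of the benefit that needs drug to be present would be reduced or gone at a scan taken after washout. A null result could then mean either that udenafil does nothing for perfusion on treatment, or that its effect had worn off before it was measured. If the two centres read the footnote differently, on-drug and off-drug scans would be pooled without anyone knowing which were which.

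**Working it through.** **Inputs, all from the protocol article**
- Stop before CMR: three days, taken as 72 h (Table 3, footnote 5).
- Half-life 11 to 13 h and duration of action about 24 h (dosage rationale).
- Daily dosing for three months (Udenafil treatment protocol).
- One post-baseline CMR, at Visit 6 (Table 3).

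**The plan's own figure.** The sample size section gives 38 per arm. Reading the responder rates as 25% with udenafil and 2% with control (the 25% is inferred, because the wording is ambiguous), with two-sided 0.05, 80% power and the pooled-variance formula:

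n = [1.96 × √(2 × 0.135 × 0.865) + 0.842 × √(0.25 × 0.75 + 0.02 × 0.98)]² / 0.23² = 33.4, so 34 per arm.

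34 / 0.9 = 37.8, so 38 per arm and 76 in total, as stated. The present point does not alter that number. It concerns whether the planned difference is measured with drug on board.

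**Drug left at the scan under the literal reading.** Assume simple first-order elimination, so that the fraction left is 0.5^(hours since last dose / half-life).

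| Time since last dose | Half-life 11 h | Half-life 13 h |
|---|---|---|
| 24 h (usual trough) | 0.5^2.18 = 22.0% | 0.5^1.85 = 27.8% |
| 72 h (footnote 5) | 0.5^6.55 = 1.1% | 0.5^5.54 = 2.2% |
| 96 h (assumed: last dose a day earlier) | 0.2% | 0.6% |

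The 72 h level is lower than the 24 h trough by a factor of 2^(48/13) = 12.9 to 2^(48/11) = 20.6. Against the stated duration of action, 72 / 24 = 3, so the scan would fall about 48 h after that duration ends.

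**Does the text settle which drugs are held?**
- For background drugs only: Table 3 labels the study product as case drug throughout. At Visit 1 the footnote can concern only background drugs, because study product is first handed out at Visit 2. Case drug collection and compliance checks run to Visit 6.
- For all drugs: the footnote's wording is unrestricted, the treatment section calls udenafil a medication, and no sentence says that study drug continues up to the scan.
- For a deliberate off-drug scan: the Background says that "the effects of chronic PDEi administration are not well known, especially in women with MVA", so interest in a lasting effect is conceivable. No section states it as the aim.

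The text therefore leaves the question open. Footnote 1 adds a smaller inconsistency: it allows no interruption of the usual regimen, whereas footnote 5 requires one on any reading.

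**The case against.** The strongest reply is that the harmful reading is the one Table 3 supports least. Within the table, medication means background therapy and the study product has its own name. A general scan-preparation note need not override a specific dosing instruction. If study drug is held on purpose, scanning under the same drug-free conditions at baseline and follow-up is a legitimate test of a sustained effect. On two of the three readings there is no design error. All of this stands, and it is why the point is conditional.

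It can also be said that scan preparation is detail a journal article leaves to the full protocol. That has less force here. The article does state a rule; the difficulty is that the rule, followed as written, conflicts with the described scheme of three months' daily dosing and a scan at the end of it.

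Two stronger conclusions might be inferred, and the document supports neither. The first is that the comparison is biased. It is not, because the hold applies equally to both arms. The second is that the trial loses a known amount of power. Figures can be produced: with assumed retained fractions of 100%, 75% and 50% of the inferred 23-point difference, Fisher's exact test at 40 per arm has power of 84%, 61% and 28%. These rest wholly on the assumed fractions. No section links drug level to perfusion response, and an effect that outlasts the drug is not excluded, so they are not evidence of the size of the problem.

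**Conclusion.** The point holds as a conditional risk. Footnote 5 can be read to include study drug, nothing in the article rules that out, and the scan it governs is the only one behind the primary endpoint. The exposure figures in the table above rest on the article's half-life and on first-order elimination. The consequence for the treatment effect cannot be quantified from the document: it ranges from nothing, if sites hold only background drugs or the effect persists, to loss of whatever part depends on drug being present. A reader should not infer that sites are in fact stopping udenafil; the article does not show what they do. Confidence is medium. The ambiguity is still worth removing, because the remedy is small and it decides which question the primary endpoint answers.

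**What to change.** First establish what the two centres do now. Then:
- Reword footnote 5 along these lines: *Udenafil/placebo continues up to the Visit 6 CMR; only background drugs are held for three days*, with the held drugs named.
- Add *except for the hold before CMR* to footnote 1.
- Record the date and time of the last study dose at Visit 6.

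If an off-drug scan is intended, keep the hold and state that the primary endpoint and its conclusion refer to an effect after washout.

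The cost is two footnotes and one case report form field, with no extra patients or procedures. Because recruitment is under way (Trial status), it also needs a minor amendment, review by both institutional review boards and a note to sites. If study drug already continues up to the scan, this is a clarification only. If some Visit 6 scans have been done off drug, changing the rule mixes two conditions; dosing status should then be recorded for the completed scans and a sensitivity analysis of the primary endpoint by that status reported.
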